#### RQ 3: process evaluation

Consistent with the Medical Research Council guidelines,^22 49^ the process evaluation will focus on contextual factors (eg, online delivery of the programme), implementation (the implementation process, fidelity, dose, adaptations and reach) and mechanisms of impact (participant responses to and interactions with the intervention).

Data will be collected from all group leaders before and after the training programme, after each session and after the end of the *Fewer Falls* programme. Data collection will include structured questions on group leader background (eg, sex, age and profession), perceived preparedness in facilitating the group and fidelity to programme manual, and semi-structured interviews. The semi-structured interviews conducted after the training programme and after the last session of the intervention will cover group leaders’ perspective on experiences of participation, contextual factors, implementation and mechanisms of impact. The interviews will be conducted face-to-face or through Zoom.

Process evaluation data will also be yielded from intervention group participants. Specifically, data will be collected from a purposively selected sample of intervention group participants (n=20–30) to represent variation in, for example, age, sex and ambulation level. Semi-structured individual interviews will be conducted by a research team member via telephone or Zoom within approximately 3, 6 and 12 months after the start of the intervention. The interviews will explore the experiences of the study participants, contextual factors and mechanisms of impact. Data from the programme platform will be collected on intervention group participants’ online activities, for example, the action plans. Participants who discontinue the intervention will be contacted and asked if they are willing to participate in a short interview to understand their reasons for not completing the programme.

#### RQ 4: health economic evaluation

Participants answering ‘yes’ to the weekly SMS inquiring about falls experienced in the last week will receive a questionnaire through the BASS database with questions on fall-related injuries, that is, healthcare utilisation, municipal care utilisation, sickness absence, medications, support from significant others and need for technical aids, including walking aids.

Estimations of resources needed to deliver the *Fewer Falls* programme will be made. Group leaders’ involvement, which includes participating in the group leader training and subsequently preparing for and delivering the *Fewer Falls* programme, will be the main programme expense. To estimate the monetary value of resource use, both for participants in the RCT and for resources needed to conduct the intervention, cost data will be retrieved from the cost per patient database held at the Swedish Association of local authorities and regions, regional price lists, as well as from Statistics Sweden. Data on quality-adjusted life years (QALYs) will be measured using the EQ-5D-5L at all timepoints.

#### Adverse events

All adverse events associated with the trial will be discussed and recorded.

### Analysis

#### Data management and statistical methods

##### RQ 1a, RQ 1b and RQ 2: effectiveness study

Intention-to-treat and per-protocol analyses will be performed. Per-protocol analyses will include participants who fulfil content adherence, defined as completion of at least two action plans.

Descriptive statistics will be used to present data, for example, means, medians, frequencies, SD, quartiles and counts. Drop-out analyses of baseline characteristics will be explored with parametric and non-parametric analyses depending on the data level.

The primary analysis for falls (falls/person/year) will be conducted using generalised linear mixed models (GLMM) with a Poisson link function to account for count data distribution and potential overdispersion. The model will include fixed effects for the intervention group and random effects for participant variations over time. Interactions between variables will be included if deemed necessary. Linear mixed model analyses will be used for normally distributed secondary outcomes. For categorical outcomes, GLMM with logistic or ordinal regression will be used, depending on the nature of the outcome (binary or ordinal). The primary endpoint is 6 months after the start of the intervention. In addition, analyses of sustainability of potential effects will be performed after 12 months. Any missing data will be handled using appropriate methods, such as multiple imputation, to ensure robustness in analyses. Analyses will be performed and reported in accordance with the Consolidated Standards of Reporting Trials (CONSORT) guidelines for RCT.^50^ A data management plan is established and stored at the Research Data Office at Karolinska Institutet.

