### Participants

The inclusion criteria for participation are self-reported diagnosis of MS; age ≥18 years; ability to walk or independently transfer from bed to chair/wheelchair with or without aids, but without assistance of another person (corresponding to ˂7.5 on the Expanded Disability Status Scale); experienced one or more falls during the last year; ability to understand and communicate in Swedish; and access to and self-rated ability to use technical devices for online meetings and falls data submission, that is, computers or tablets with internet access and mobile phones to receive and send short message service (SMS).

The statistical power calculation for the primary outcome, fall frequency, is based on data from our feasibility pilot RCT study (in manuscript). The pilot study included 45 participants, randomised into an intervention or control group. Falls were monitored weekly via SMS for 18 weeks from the start of the intervention. Data from 27 participants who at baseline reported a fall within the previous 3 months were used. Based on the findings of 2.45 falls for the intervention group (n=11) versus 3.69 in the control group (n=16) over a period of 18 weeks, we determined that a sample size of 84 participants per group is necessary to achieve adequate statistical power (0.8, alpha=0.05).^28^

Because an online publication on interventions for people with chronic conditions reported a high attrition and drop-out rate,^29^ we aim to recruit up to 240 participants, allowing for up to a 35% drop-out rate. The sample size is based on a Poisson distribution, which aligns with the nature of our primary outcome falls/person/year.

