The intervention is delivered to groups of approximately eight participants. A health professional (ie, a physiotherapist, occupational therapist or social worker) recruited via the researchers’ network facilitates the online synchronous group sessions. Seven group leaders will be recruited to lead one or two cycles (ie, seven sessions followed by one booster session) of the programme in concurrently ran groups. The research team recognise the importance of involving several group leaders to allow for effective assessment of programme fidelity and reduce the possibility that successful programme outcomes would be attributed to the skill set of one or two group leaders. Approximately 15 cycles of the *Fewer Falls* programme will be run. The group leaders will not be involved in the usual care of the participants.

The group leaders will complete an extensive online training programme before delivering *Fewer Falls*. This training programme will consist of asynchronous online modules. Collectively, these modules (a) describe the aim, structure, content and theoretical foundation of *Fewer Falls* as well as the role of the group leaders; (b) provide an overview of MS, falls and fall risk factors for PwMS; (c) orient group leaders to the *Fewer Falls* group leader manual; and (d) provide detailed descriptions of content and process of *each programme* session. Each module of the training programme ends with a quiz or a reflective question. The final module of the training programme consists of a synchronous online role-play session. In addition, the group leaders will receive instructions on how to use the digital tools used during the *Fewer Falls* programme.

To ensure participant adherence to the programme, the group leaders will contact participants who missed one session. If participants miss two sessions in a row, the research assistant will contact the participants.

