### Theoretical basis, self-management approach and pedagogical model

The leading theory informing the *Fewer Falls* programme content and process is the Social Cognitive Theory (SCT).^31 32^ Reciprocal determinism, the central concept of SCT, refers to the dynamic and reciprocal interaction of person (with learnt experiences), environment (external social context) and behaviour (responses to stimuli to achieve goals).^32^ Reciprocal determinism is applied in *Fewer Falls* because participants, with their respective experiences, work together to learn about fall risks and management strategies and change their behaviours to reduce their risk of falling. The SCT components of observational learning and reinforcements align well with the programme’s focus on group format; participants are learning and receiving feedback from peers. According to SCT, self-regulation refers to the ability to understand and manage own behaviours.^32^ In *Fewer Falls*, self-regulation supporting the reduction of fall risk is fostered through using two to four action plans. Through each action plan, participants identify and explain a specific fall risk, a strategy to address that fall risk, their level of confidence in implementing that strategy, the deadline for completion and resources to support their success in implementing the strategy. Each action plan includes a section for participants to evaluate the extent to which the planned strategy was implemented. Participants are given the opportunity to report on the status of their action plans and work together to refine action plans as needed. Self-efficacy, a central component in SCT, is described as a possible mechanism by which self-management is achieved.^33^ An important goal of *Fewer Falls* is to build participants’ falls self-efficacy.

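### The stated primary model names no term for programme group, although only the intervention arm is treated in groups; if outcomes correlate within groups, the standard error is too small.

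*Protocol article*

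**What the plan says.** Under Recruitment and procedures, participants are randomised individually, 1:1, stratified by ambulation. Under Control, the comparison arm receives a brochure on top of standard care, with no group element.

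Under Intervention, "The intervention is delivered to groups of approximately eight participants". About 15 cycles are planned, run by seven leaders who each take one or two. Several leaders are used partly to "reduce the possibility that successful programme outcomes would be attributed to the skill set of one or two group leaders". The theory section describes the group format as a route of effect: "participants are learning and receiving feedback from peers".

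Under Data management and statistical methods (RQ 1a, RQ 1b and RQ 2), the primary analysis of falls is a Poisson generalised linear mixed model. Its terms are given: "The model will include fixed effects for the intervention group and random effects for participant variations over time". Interactions may be added if judged necessary. For secondary outcomes only the model families are named.

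Under Participants, the sample size rests on "2.45 falls for the intervention group (n=11) versus 3.69 in the control group (n=16) over a period of 18 weeks", from which "a sample size of 84 participants per group is necessary" at power 0.8 and alpha 0.05. No ICC or design effect is mentioned.

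**The concern.** This is a partially nested design: people in the intervention arm share a group and a leader, and people in the control arm share neither. A participant-level random effect absorbs overdispersion between people and correlation among one person's repeated counts. It treats two members of the same group as independent.

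If their outcomes are positively correlated, the intervention-arm mean is less precise than the model reports. The interval for the rate ratio is then too narrow and the p-value too small, which favours declaring the programme effective. The article itself gives reasons why correlation is plausible: peer learning, shared leaders, and discussions whose focus depends on the members' priorities.

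This is more than detail left to an analysis plan, because the article does state a random structure and that structure does not match the design.

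**Working it through.** **The plan's own sample size.** Two-sided alpha is assumed, as the article does not state sidedness. (1.96 + 0.84)² = 7.849.
- Difference scale: 7.849 × (2.45 + 3.69) / (3.69 − 2.45)² = 31.3.
- Log scale: 7.849 × (1/2.45 + 1/3.69) / ln(3.69/2.45)² = 31.8.

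A plain Poisson comparison therefore needs 32 per group. The stated 84 is not reproduced; it implies a further variance factor of 84/31.8 = 2.64 that the article does not explain. Below, 84 per group is taken as giving power 0.80.

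**Inputs for the clustering check**
- Group size 8 (Intervention section); 15 × 8 = 120, which is one arm of 240.
- Drop-out: "we aim to recruit up to 240 participants, allowing for up to a 35% drop-out rate". If those lost leave the analysis evenly, 8 × 0.65 = 5.2 remain per group.
- Seven leaders: 120/7 ≈ 17 participants per leader.
- ICC: assumed 0.01 to 0.10, as the documents give none.

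**Formulas** (equal arms, equal total variance, clustering in one arm)
- Design effect in the intervention arm: DE = 1 + (m − 1) × ICC.
- True over assumed variance of the contrast: V = (1 + DE)/2.
- True two-sided level: 2 × [1 − Φ(1.96/√V)].
- Power once the standard error is right: Φ(2.80/√V − 1.96).

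Example, m = 8 and ICC 0.05: DE = 1 + 7 × 0.05 = 1.35; V = 1.175; √V = 1.084; 1.96/1.084 = 1.81; level 7.1%.

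| ICC | DE (m = 8) | SE ratio √V (m = 8) | Level, m = 8 | Level, m = 5.2 | Level, by leader (m ≈ 17) |
|---|---|---|---|---|---|
| 0 | 1.00 | 1.00 | 5.0% | 5.0% | 5.0% |
| 0.01 | 1.07 | 1.02 | 5.4% | 5.2% | 5.9% |
| 0.02 | 1.14 | 1.03 | 5.8% | 5.5% | 6.9% |
| 0.05 | 1.35 | 1.08 | 7.1% | 6.2% | 9.8% |
| 0.10 | 1.70 | 1.16 | 9.2% | 7.5% | 14.5% |

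With full groups, a nominal 95% interval correspondingly covers about 94.6% at ICC 0.01 and 90.8% at 0.10.

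**Simulation.** 20,000 trials per ICC; 120 per arm; 15 groups of 8; overdispersed Poisson counts; log ratio of arm means tested as if participants were independent; ICC on the latent log-rate scale. Rejection rates were 5.3% at ICC 0, 5.8% at 0.01, 6.7% at 0.05 and 8.0% at 0.10. The direction is the same and the size somewhat smaller, partly because the ICC is defined on another scale.

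**Power.** Taking 0.80 at 84 per arm:
- Full groups of eight: 0.79, 0.77, 0.73 and 0.67 at ICC 0.01, 0.02, 0.05 and 0.10; 84 per arm would become 87, 90, 99 and 114.
- If the 84 are spread over 15 groups (5.6 each): 0.79, 0.78, 0.76 and 0.71; 84 would become 86, 88, 94 and 104.

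**The case against.** The strongest reply is that the size of the problem rests wholly on an assumed ICC. If the programme changes nothing for anyone, individually randomised people acquire no correlation from delivery, and the test keeps its 5% level. Inflation under a null average effect needs group effects that differ but average to zero. A manual, common leader training and fidelity monitoring would all tend to lower the ICC, and drop-out shrinks the groups. This stands, so the consequence must be stated as conditional.

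Several stronger readings are tempting, and the article does not support them:
- A reader might infer that the random effects are for participants and nothing else. The article lists what the model will include; it does not say the list is complete, and an analysis plan not shown could add a term. As published, none is named.
- A reader might infer that the secondary analyses carry the same error. No random structure is stated for them, so no error is fixed there.
- A reader might infer that the authors expect leader effects. The remark on leaders explains a design safeguard. Using several leaders spreads such an effect but does not put it into the standard error.
- A reader might infer that the groups are closed to new members. The text does not say so.
- A reader might infer that the sample size certainly ignores clustering. The article is silent on it, and 84 contains an unexplained factor.

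None of this supplies the missing group term. The allowance for interactions does not do so either: an interaction between covariates is not a variance component for groups.

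**Conclusion.** The point holds in conditional form. The stated primary model does not match a design in which one arm only is grouped. For a within-group ICC between 0.01 and 0.10, the true two-sided level is about 5.4% to 9.2% with full groups of eight, and about 5.2% to 7.5% with 35% drop-out spread evenly. It is 5% at ICC 0. The effect is slight at 0.01 and material from about 0.05, or sooner if correlation runs by leader.

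The documents do not support saying that the false-positive rate definitely exceeds 5%, because they give no ICC. The figures also assume equal arms, equal total variance and groups of equal size. The direction does not depend on the exact ICC: any positive value makes the standard error too small.

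**What to change.** Before outcome data are analysed, specify the primary falls model as partially nested:
- Add a random effect for programme group that operates in the intervention arm only, with each control as its own cluster.
- Define group by assignment, whatever the attendance, so that it fits the intention-to-treat analysis.
- Use small-sample degrees of freedom suited to about 15 groups.
- Use the same structure when the secondary mixed models are specified.
- Treat leader as an exploratory sensitivity analysis only. With seven leaders taking one or two cycles each, leader and group are nearly confounded and a leader variance would be poorly estimated.
- Restate power over an assumed ICC range, with the basis of the 84 per group made explicit.

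The cost is one variance term and slightly wider intervals; if the ICC is near zero, little precision is lost. Group membership should be known from delivery, although the article does not say that it is recorded for analysis. Fixing the term in advance matters because adding or dropping it after seeing results would be a data-driven choice.

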## Introduction

 Multiple sclerosis (MS) is a chronic inflammatory, demyelinating and neurodegenerative disease that typically is progressive in nature.^1^ Several symptoms of MS are known fall risk factors, including impaired balance, gait and cognition.^2 3^ In people with MS (PwMS), approximately 56% experience a fall within 3 months.^4^ Those PwMS who have experienced a fall in the past year have an 82% probability of falling again within 6 months and a 56% probability of an injurious fall.^5^ Falls among PwMS are associated with fear of falling, low health-related quality of life and injuries.^3 6^ Because PwMS frequently experience injurious falls,^7^ the socioeconomic costs for both PwMS and society are potentially high. Surprisingly, there are no studies on costs related to falls in PwMS. However, existing research describing the cost of falls for other patient populations with neurological problems ^8 9^ have suggested the high healthcare costs associated with falls among PwMS.

Despite the recognition that several MS symptoms influences fall risk,^2 3^ most fall prevention interventions for PwMS only address physical impairments. There is a major gap in existing evidence regarding behavioral and environmental influences on fall risk in PwMS. The importance of comprehensive approaches to fall prevention targeting modifiable risk factors through fall prevention programmes for PwMS has been highlighted.^10^ Another major gap in MS falls research is the scarcity of studies that focus on falls among the 25% of the MS population who can walk only a few steps or not at all, ie, are non-ambulatory.^6^ Fall prevention interventions for non-ambulatory PwMS show promising results but are rare.^11 12^ Although ambulatory and non-ambulatory PwMS share the same fall risk factors,^2 13^ new evidence suggests that some fall risk factors are unique to non-ambulatory PwMS.^13^ Thus, fall prevention programmes for PwMS must target the unique needs and multifactorial fall risks of PwMS, with consideration that members of the target audience may be ambulatory or non-ambulatory and typically will experience fluctuations in functional status and disease over time.

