### Recruitment and procedures

Participants will be recruited via flyers placed in inpatient and outpatient MS and rehabilitation clinics, from social media advertisements published by Karolinska Institutet, and by the patient organisation Neuro Sweden.

The notices will include a link to a webpage with study information and an online template where interested individuals can fill in their contact information. A research assistant with training in Good Clinical Practice^30^ will screen the completed templates regularly, contact potential participants by phone or e-mail (depending on PwMS’ choice of contact), and provide potential participants with information about the study. Individuals expressing interest in the study will be screened for eligibility. The informed consent process will be initiated with PwMS who meet the eligibility criteria. Specifically, eligible PwMS will be sent written information. Informed consent (online supplemental material) is obtained through BASS, an integrated online treatment and assessment platform. The platform is provided by the eHealth Core Facility at Karolinska Institutet, Stockholm, Sweden. Individuals providing informed consent will be included.

Baseline assessment will be supported by the use of the BASS database. The PwMS will subsequently be randomised to the intervention group or the control group using a data-generated system (Sealed Envelope Ltd. 2021). Participants will be stratified as non-ambulatory (able to walk a maximum of 5 m with assistance or not able at all) or ambulatory in a 1:1 allocation ratio of blocks of eight. Participants will be contacted by phone to inform them about group allocation.

Recruitment began in December 2023, and the expected completion of the study is January 2027. An overview of the study schedule of enrolment, allocation, intervention and assessments are presented in figure 1.

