### Data collection and outcome measures

#### RQ 1a, RQ 1b and RQ 2: effectiveness study

Data will be collected using the digital platform BASS database. The data collection will be blinded as the participants receive a link to the BASS database, which provides them with access to the questionnaires that are completed online. Baseline data includes the sociodemographic information (ie, age, sex, civil status, work status and educational level); disease-related characteristics (ie, MS severity, time since diagnosis, symptoms, medications and other treatments, other diagnosis and aids); formal/informal care; cognitive function (collected through the short version of the Montreal Cognitive Assessment Scale^36^); anxiety and depression (collected through the Hospital Anxiety and Depression scale^37^); fatigue (assessed by the Fatigue Severity Scale^38^); health literacy (assessed via the Swedish version of the Health Literacy Survey European Questionnaire/16 item version^39^); self-reported falls and fall related injuries in the previous 6 months; and expectations on the programme.

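### The primary falls model names no baseline covariate, although prior falls are collected at baseline and not balanced by the randomisation; prespecifying them would gain precision at almost no cost

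*Protocol article*

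**What the plan says.** All references are to the protocol article.

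- **Model family** (Analysis, RQ 1a, RQ 1b and RQ 2). The primary analysis uses "generalised linear mixed models (GLMM) with a Poisson link function to account for count data distribution and potential overdispersion".
- **Model terms** (same section). "The model will include fixed effects for the intervention group and random effects for participant variations over time". The next sentence adds: "Interactions between variables will be included if deemed necessary". No baseline covariate is named.
- **Baseline data** (Data collection and outcome measures, RQ 1a, RQ 1b and RQ 2). The list includes "self-reported falls and fall related injuries in the previous 6 months". This window is as long as the one for the 6-month primary endpoint.
- **Randomisation** (Recruitment and procedures). "Participants will be stratified as non-ambulatory (able to walk a maximum of 5 m with assistance or not able at all) or ambulatory". Prior falls are not a stratification factor.
- **Eligibility** (Participants). Entrants must have "experienced one or more falls during the last year", with no upper limit stated.

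Nowhere does the article give baseline falls a role in the primary analysis.

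**The concern.** Eligibility admits both a person with one fall eleven months ago and a person who falls every week. Such differences between people widen the interval for a fall rate ratio. If falls in the previous 6 months predict later falls, including them in the model removes part of that variation. The participant random effect does not do this job: it lets the standard error reflect the variation, but it neither explains it through prior falls nor corrects a difference between the arms.

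Two things are at stake. One is power, in a trial that would keep 78 per arm at its own drop-out allowance. The other is how far the single estimate can be trusted if, by chance, more frequent fallers land in one arm.

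**Working it through.** **Inputs from the article (Participants).** The pilot gave "2.45 falls for the intervention group (n=11) versus 3.69 in the control group (n=16) over a period of 18 weeks", so the rate ratio is 2.45/3.69 = 0.664 and its log is -0.4095. The stated size is 84 per group for power 0.8 at alpha 0.05; the number of sides is not given, and two-sided is assumed here. The recruitment target is 240 with up to 35% drop-out: 240 x 0.65 = 156, or 78 per arm.

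**The plan's own figure.** Plain Poisson on the log scale:

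n = (1.960 + 0.842)² x (1/2.45 + 1/3.69) / 0.4095² = 7.849 x 0.679 / 0.1677 = 31.8, or 32 per group.

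This does not reproduce 84. To reach 84, a between-person dispersion k (variance = m + k m²) is needed:

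k = (84 x 0.1677/7.849 - 0.679)/2 = 0.56.

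The mismatch is a separate matter. It is used here only to set the low end of the assumed k.

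**Assumed, because the article gives neither:** k = 0.56, 1 and 2; correlation of a person's log fall rates before and after baseline = 0.4, 0.7 and 0.9. Pilot rates are carried forward at a constant rate to 26 weeks: 2.45 x 26/18 = 3.54 and 3.69 x 26/18 = 5.33.

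**Analytic check.** Let f be the share of between-person dispersion that prior falls explain. Then

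n per arm = 7.849 x [1/3.54 + 1/5.33 + 2k(1 - f)] / 0.1677.

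- k=0.56: f=0 gives 75; f=0.5 gives 49.
- k=1: f=0 gives 7.849 x 2.470/0.1677, or 116; f=0.5 gives 7.849 x 1.470/0.1677, or 69.
- At 78 per arm and k=1, power is 0.63 with f=0 and 0.85 with f=0.5.

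**Simulation.** 78 per arm, 26 weeks, true rate ratio 0.664, lognormal person rates, 1,000 trials per setting. A Poisson regression with robust standard errors stands in for the mixed model, without and with log(baseline falls + 0.5).

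| k | Correlation | Variance cut | Power without | Power with |
|---|---|---|---|---|
| 0.56 | 0.4 | 4% | 0.82 | 0.84 |
| 0.56 | 0.7 | 27% | 0.81 | 0.90 |
| 0.56 | 0.9 | 37% | 0.84 | 0.95 |
| 1 | 0.4 | 6% | 0.67 | 0.68 |
| 1 | 0.7 | 28% | 0.65 | 0.81 |
| 1 | 0.9 | 49% | 0.65 | 0.90 |
| 2 | 0.4 | 6% | 0.48 | 0.52 |
| 2 | 0.7 | 34% | 0.48 | 0.62 |
| 2 | 0.9 | 58% | 0.50 | 0.80 |

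A repeat simulation gave cuts of about 20-46% at correlation 0.7 and about 1-12% at 0.3, so those wider ranges are the ones to quote. Robust standard errors matter here. Model-based negative binomial standard errors on such data came out at about 0.75 to 0.9 of the true spread for k = 1 to 2, which overstates power.

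**Chance imbalance.** Suppose k=1 and a baseline mean of 5.33 in both arms. The log ratio of the arms' mean prior falls then has standard deviation sqrt(2 x (1/5.33 + 1)/78) = 0.174. A difference of about 19% or more (exp 0.174 = 1.19), in either direction, would occur in about one trial in three.

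In the 16% of simulated trials with the largest imbalance against the intervention arm:

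- True rate ratio 0.66: estimated at 0.70-0.82 unadjusted and 0.66-0.68 adjusted.
- True rate ratio 1, correlation 0.7: estimated at 1.09 (k=0.56) and 1.17 (k=2) unadjusted, against 1.00 and 0.99 adjusted.

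Over all trials the unadjusted estimate is centred on the truth. Type I error hardly changes without and with adjustment: 0.056 and 0.058 at k=0.56, 0.073 and 0.074 at k=2.

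**The case against.** The best defence is that the model sentence is a sketch. It says what the model will include, not that nothing else enters. It mentions no exposure term, no time term and no ambulation stratum, and the following sentence allows interactions, for which group alone has no partner. Covariates are often listed in an analysis plan, which is not shown. This stands to a degree: a reader might infer that group is the only fixed effect, and the text does not say so. But the article does set out the model's content, and an open clause about interactions prespecifies no adjustment.

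Four other inferences go too far.

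- **That the unadjusted analysis is biased.** It is not. Randomisation makes it valid on average, and its interval already allows for chance imbalance. The loss is in precision and in accuracy given the imbalance that actually occurs.
- **That the Introduction proves prior falls to be a strong predictor in this trial.** It reports that people with a fall in the past year "have an 82% probability of falling again within 6 months". Every participant meets that condition, so the figure cannot separate higher from lower risk within the trial, and it says nothing about a gradient by number of falls.
- **That a count is already in hand.** The baseline item is not described as a count, categories or yes/no.
- **That a large gain is assured.** Baseline falls are recalled over 6 months and follow-up falls are reported weekly by SMS. The simulation gives recall no error, so the low correlations deserve weight. The pilot rates also come from 27 people with a fall in the previous 3 months, a narrower group than those eligible.

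**Conclusion.** The point holds as one of efficiency. The article describes a primary model with no baseline covariate while collecting an obvious candidate that the randomisation does not balance. Nothing in the stated analysis is invalid.

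The gain ranges from negligible to substantial: about 1-12% of the variance of the log rate ratio at a correlation of 0.3-0.4, roughly 20-45% at 0.7, and more at 0.9. At k=1 and correlation 0.7, power goes from about 0.60-0.65 to about 0.8. These figures rest on assumed dispersion and correlation, pilot rates held constant to 26 weeks, and a two-sided test. The direction is secure provided that prior falls predict later falls at all; the size cannot be settled from the article.

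**What to change.** Before unblinding, add one sentence to the description of the primary model in the Analysis section, and to the analysis plan if there is one: *The model will also include a prespecified fixed effect for falls in the 6 months before baseline.*

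- If the item is recorded as a count, enter log(count + 0.5). The 0.5 handles people whose only qualifying fall was 7 to 12 months ago and who therefore have a count of zero. If it is recorded in categories, enter those categories.
- Use the same model for the 12-month analysis.
- Report the model without this covariate as a sensitivity analysis.

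This is a free improvement. The item is already collected, and the cost is one degree of freedom for a count or a few for categories. The article says that protocol updates will be registered, so the change can be dated before unblinding.
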